### Data collection methods

#### Delivery observations

Data will be collected through observation of health worker practices at baseline, midline and end line. Observations will be conducted by a team of four observers with clinical expertise so that they will be knowledgeable about clinical issues and capable of providing accurate assessments of whether SCC practices are completed or not. Observations will be conducted for a minimum of 3 days in all facilities, or as long as required to observe at least seven births.

It may not be possible for the observer to document every delivery process at all times, particularly if multiple deliveries are taking place at one time, so observations will relate to activities at four specific periods (pause points). As a part of the training process, the observing data collectors will observe births in parallel with a trainer or supervisor to ensure accuracy and consistency in recording the necessary information. Data collectors will be trained to recognize each of the practices on the checklist according to the definitions adapted from previous work [8]. Observation data will be recorded on standardized data sheets over the course of the delivery process. Data will be collected on paper forms and later entered electronically on portable touch-screen tablets that each observer will be equipped with.

#### Health worker questionnaires

A self-administered questionnaire [14] will be administered to health workers at the end of the facility-based SCC training and after all end line observations are completed to understand the overall success and acceptability of the tool and supportive activities. The questionnaires will collect basic information about the participant, their feedback on the process of using the SCC, and the appropriateness of the SCC for Zambia.

### Statistical methods

For the primary outcome, data from each delivery will be considered as a percentage of the 21 SCC items that were practiced, or in other words each pause point observation will be assigned a score from 0 to 100%. The differences over time will be examined using linear regression and accounting for clustering at the facility level as well as transformation to account for the bounded data. We will also consider clustering at the level of the primary provider responsible for overseeing the delivery. Sub-analysis will be conducted to account for the impact of availability of supplies on conduct of tasks. Within each facility in the sample, we will also compare the average score for all deliveries at baseline, midline and end line using a paired, weighted t-test to account for differences in the standard errors. Finally, to better explore meaningful change due to the program, we will examine if there is an increase in the proportion of births where the majority (75%) of tasks are completed; specifically, we will examine if the difference overtime in the average proportion of births where 75% of tasks were completed increases due to the intervention. To this end we will run individual-level logistic regression, accounting for clustering at the facility level.

For the health worker questionnaires, we will report descriptive statistics only, with baseline and end line comparisons.

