### Outcomes

The primary outcome variable of interest is the change in the average proportion of essential childbirth practices completed per birth out of those observed from the list of selected tasks. We have developed a list of selected tasks that represent a sub-set of items in the SCC which are tasks that can be visually observed and that are non-conditional (in other words they should be performed on all mother-infant pairs regardless of health status). The list of selected tasks includes the following 21 items:Was vaginal exam performed to check dilation?Were sterile gloves used for the vaginal exam?Was partograph started?Did the health worker review danger signs with the mother (and companion)?Were water and soap used to clean hands alcohol rub used on the mother just before delivery?Were sterile gloves used at the time of delivery?Were all of the following supplies available at the bedside? (Clean scissors or blade, Clean cord tie or clamp, Aspiration bulb or mucus extractor, Neonatal bag and mask, Oxytocin 10 units in syringe)Did the primary health worker managing the delivery communicate with a health worker assistant to say that the birth will happen shortly and ask for assistance?Was oxytocin administered?Was newborn weight taken?Was newborn temperature taken within 1 h after birth?Was baby placed skin-to-skin on mother’s abdomen?Was breastfeeding initiated?Was maternal temperature obtained at admission?Was maternal blood pressure obtained at admission?Was maternal blood pressure obtained at discharge?Was maternal temperature obtained at discharge?Was newborn temperature taken at discharge?Did health worker confirm that infant is feeding well?Did health worker discuss family planning options with mother?Did health worker plan a follow-up visit for mother and newborn and discuss danger signs?

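### The primary score has inconsistent definitions (per birth over items observed, per delivery over a fixed 21, per pause point), and the fixed-21 wording can count unobserved items as not done

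*Protocol article*

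**What the plan says.** Three places in the protocol article bear on the primary score.

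- **Outcomes** gives the primary outcome as "the change in the average proportion of essential childbirth practices completed per birth out of those observed from the list of selected tasks". The unit is the birth, and the denominator follows what was observed. The same section says "The list of selected tasks includes the following 21 items" and describes the items as visually observable and non-conditional.
- **Statistical methods** treats the data from each delivery "as a percentage of the 21 SCC items that were practiced, or in other words each pause point observation will be assigned a score" between 0 and 100%. In the first half of that sentence the unit is the delivery, and the denominator is 21. In the second half, offered as a restatement, the unit is the pause point, of which a birth has up to four.
- **Delivery observations** warns: "It may not be possible for the observer to document every delivery process at all times", particularly when deliveries overlap. Its response is that "observations will relate to activities at four specific periods (pause points").

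The article does not say which definition governs or how an unobserved item is scored. Statistical methods also sets an endpoint based on completing 75% of tasks, without stating its denominator.

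**The concern.** The observed-item score and the fixed-21 score agree only when all 21 items are seen in every birth, and the plan does not expect that. Under a literal fixed 21, an item that the observer could not see adds nothing to the numerator but stays in the denominator, so it acts as a failure by the health worker. The same happens to an item that cannot apply, such as gloves for a vaginal examination that was not done. If coverage differs between baseline and a later round, a change in observation would be read as a change in practice.

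The pause-point version differs even with complete observation. It gives each pause point equal weight whatever its number of items, and it yields several correlated scores per birth, whereas the clustering named in Statistical methods is by facility and provider only.

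This is the primary outcome of a pilot meant to inform national adoption. Leaving its definition open also leaves room to choose one after the data are seen.

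**Working it through.** **The plan's own figure.** Sample size gives z values 1.96 and 0.84, s = 17% in both periods, ρ = 0.25, n = 6.5, and means of 34% and 58%. With its formula:

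c = 1 + (2.80)² × [(0.17² + 0.17²) × (1 + 5.5 × 0.25)] / [6.5 × 0.24²] = 1 + 1.0762/0.3744 = 3.87, rounded up to 4 facilities.

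Solved for the difference at c = 4: √(1.0762 / (6.5 × 3)) = 23.5 points, stated as 24. The figure reproduces, so the power arithmetic is not at fault here. I use 34% and 58% below as the reference levels.

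**Grouping of items (my assumption).** The article does not assign the 21 items to pause points. By wording I get admission 6, before delivery 4, after birth 5, discharge 6; the sum is 21.

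**Ceiling for the 75% endpoint.** 75% of 21 is 15.75, so 16 items are needed. With one block unseen and counted as not done, the highest possible score is:

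- admission or discharge unseen: 15/21 = 71.4%, so 75% is out of reach
- after birth unseen: 16/21 = 76.2%
- before delivery unseen: 17/21 = 81.0%

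**Effect on the change over time.** Let p be true adherence, equal across items, and f the share of births with discharge unseen. The fixed-21 mean is p × (1 − f × 6/21), and the observed-item mean stays at p. The documents give no f, so these are scenarios.

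- Endline only, f = 20%: 0.58 × (1 − 0.2 × 6/21) = 0.547. The 24-point change reads as 20.7. With no true change: 0.34 × 0.943 − 0.34 = −1.9 points.
- Endline only, f = 50%: 0.58 × (1 − 0.5 × 6/21) = 0.497. The change reads as 15.7. With no true change: −4.9 points.
- Baseline only, f = 50%: 0.58 − 0.291 = 28.9 points, so the effect is overstated.
- Both rounds, f = 50%: 0.497 − 0.291 = 20.6 points. With no true change: 0.

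**Pause-point weighting, everything observed.** A 60-point gain confined to the four-item block moves the item-based score by 0.60 × 4/21 = 11.4 points and the mean of four pause-point scores by 0.60/4 = 15.0 points. This is a deliberately uneven example, used only to show that the two scores are not the same.

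**Does an observed-only denominator remove the problem?** Not entirely. Suppose overall adherence is 34% and discharge items are done 10% of the time (assumed). The other 15 items then average (0.34 × 21 − 0.10 × 6)/15 = 43.6%. With discharge unseen in 20% of births:

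- observed-only: 0.8 × 34.0 + 0.2 × 43.6 = 35.9%, a shift of +1.9 points
- fixed 21: 0.8 × 34.0 + 0.2 × (6.54/21 = 31.1%) = 33.4%, a shift of −0.6 points

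When items differ in difficulty, the observed-only score also moves with coverage.

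**The case against.** The strongest reply is that this is one loose clause. Outcomes says per birth. Statistical methods opens with the delivery, then compares average scores over deliveries, counts births reaching 75%, and uses individual-level logistic regression. No analysis is stated at pause-point level. That stands: a reader might infer that three separate endpoints will be analysed, and the text does not support it.

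Secondly, the observed tasks in Outcomes could mean the tasks selected for observation, which would match the fixed 21. The reading is possible, but it settles the denominator without saying what happens to an item nobody saw, so the gap remains.

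Thirdly, the article nowhere says that unobserved items count as not done. Such coding is often left to data sheets or an analysis plan, and neither is shown. That also stands. The fixed-21 wording permits that scoring but does not prescribe it, and it cannot be said that the data sheets fail to make the distinction.

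Fourthly, the pause points are themselves the plan's response to incomplete observation. They limit the problem, but a whole pause point can still be missed.

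Finally, a reader might infer that the rule of at least 3 days or seven births makes coverage differ between rounds. It applies to every round, so it is no reason for a difference by itself.

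**Conclusion.** The inconsistency in the definition of the primary score is in the current text and does not depend on any assumption. Two of the conflicting versions are joined in one sentence as though equivalent.

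The consequences are conditional. The 71.4% ceiling needs the literal fixed-21 scoring and my grouping of about six items at admission or discharge. It affects the 75% endpoint, which the plan presents as a further exploration and not as the primary outcome. The distortion of the change over time needs coverage that differs between rounds or, for shrinkage of a true effect, coverage that is incomplete in both. For discharge missed in 20% to 50% of endline births only, 24 points reads as about 20.7 to 15.7, and a null as about −1.9 to −4.9. The opposite pattern would inflate the effect, and equal missingness with no true effect creates no false change. It would go beyond the documents to say that the result will be biased, or by how much.

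Outcomes says nothing about applicability; it calls the items non-conditional. A rule for items that cannot apply is therefore an addition to its definition.

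**What to change.** In Statistical methods, state one score per birth: items done divided by items observed, as in Outcomes. Delete the fixed-21 and pause-point wording, and use the same score for the 75% endpoint.

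Add three things:

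- Items that cannot apply, such as gloves when no vaginal examination was done, leave the denominator. The data sheet should record not observed and not applicable separately from not done.
- Report the number of items observed per birth by round, because the observed-only score also shifts with coverage when items differ in difficulty.
- Run one sensitivity analysis limited to births observed at all four pause points. Show pause-point scores descriptively only.

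The cost is a few sentences, one sensitivity analysis, and a check of the response codes on the data sheet. No additional births are needed. The remaining downside is the small coverage dependence of the observed-only score, which the last two additions make visible.

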### Study setting

The WHO SCC will be introduced in eight purposively selected health facilities in Nchelenge District, Luapula Province. Nchelenge District was chosen by the MOH to be the location for this pilot based on need. The eight facilities were selected based on criteria including: high demand for services, perceived need for support for quality improvement, and presence of a SBA to mentor. However, data collection for this evaluation will take place in only four facilities with high volumes for the observations to occur. The four sites include three health centers and one general hospital.

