### Sample size

We calculated the expected power that this observation period will give us to detect changes in practices based on data about delivery volumes at the four sites, using the following formula [22]:

$$ c=1+{\left({z}_{\alpha /2}+{z}_{\beta}\right)}^2\ast \frac{\left[\left({s}_0^2+{s}_1^2\right)\ast \left(1+\left(n-1\right)\rho \right)\right]}{n{\left({m}_0-{m}_1\right)}^2} $$

Due to the small number of facilities the equation utilizes the difference in the main proportion assuming a t-test will be utilized [23]. Where: c = number of facilities needed, Z_a/2_ and Z_B_ = type I (1.96) and type II error (0.84) respectively, s_0_ and s_1_ are the standard error at baseline (17%), ρ = interclass correlation (0.25). We estimate that at baseline 34% (m_0_) of the 15 SCC items will be observed per birth, based on previous work in India indicating that an average of 9.8 out of 29 items were observed per birth at baseline [12]. According to the Health Management Information System data from January to October 2016, there was an average of 390 deliveries per month across the four study facilities. This means that if we observed all deliveries for approximately 48 h in each site, we could expect to observe an average of 6.5 (n) deliveries per site. With such a sample size, the calculations indicate that we could detect an absolute increase of 24% in the proportion of adherence to SCC essential best practices (m_1_ = 58%).

For the secondary outcomes related to health workers characteristics and feedback, all health workers in the four study sites will be invited to participate as a convenient sample.

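### With only four facilities, the clustered linear and logistic regressions carry no few-cluster safeguard, although the sample size assumes a t-test for that very reason

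*Protocol article*

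**What the plan says.** The protocol article, Study setting, restricts the evaluation: "data collection for this evaluation will take place in only four facilities with high volumes". Its Sample size section draws a consequence from this: "Due to the small number of facilities the equation utilizes the difference in the main proportion assuming a t-test will be utilized". The formula there uses normal quantiles ("type I (1.96) and type II error (0.84) respectively"), but it adds one facility to the computed number, which works as an allowance for few clusters.

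The Statistical methods section then analyses single deliveries. For the primary score: "The differences over time will be examined using linear regression and accounting for clustering at the facility level", with a transformation because the score is bounded. For the proportion of births with 75% of tasks done: "To this end we will run individual-level logistic regression, accounting for clustering at the facility level". Neither sentence names a variance estimator, a reference distribution or degrees of freedom. Clustering by the primary provider will also be considered.

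A t-test does appear in the same section, as an additional comparison. It is introduced with "Within each facility in the sample, we will also compare the average score for all deliveries at baseline, midline and end line" and is described as paired and weighted to allow for unequal standard errors.

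**The concern.** The Sample size section treats four facilities as a reason for a t-test. The section that fixes the primary analysis does not repeat that caution. Common ways of carrying out a regression clustered on facility rely either on many clusters (a sandwich variance with normal critical values, the usual GEE default) or on facility effects that do not move between rounds (a facility intercept with model-based errors). With four facilities the first fails, and the second cannot be checked well. Providers work within facilities, so clustering on provider does not add independent facilities.

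There is no control group, so the interval for the before-after change is the only statistical guard against reporting a chance shift as improvement. The Discussion says the results are meant to inform national adoption of the checklist.

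**Working it through.** **Inputs from the article.** Four facilities (Study setting). SD 17%, ICC 0.25, n = 6.5 births per site, 34% to 58%, z values 1.96 and 0.84 (Sample size; the 17% is called a standard error there but acts as an SD in the formula). At least seven births per facility (Delivery observations).

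**Assumed, because the article gives no figure.** The correlation r of a facility's effect between two rounds (1, 0.8, 0.5, 0). Unequal volumes of 7 to 20 births per facility and round. For the logistic model, an event rate near 30% and a latent ICC of 0.25. Scores are taken as normal and untransformed, and two rounds are compared.

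**1. The plan's own figure reproduces.**
c = 1 + 2.8² × [2 × 0.17² × (1 + 5.5 × 0.25)] / (6.5 × 0.24²) = 1 + 1.0762 / 0.3744 = 3.87, so four facilities.
Solved for the difference with c = 4: √(1.0762 / (6.5 × 3)) = 0.235, consistent with the stated 24 points.

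**2. Sandwich variance, equal volumes, exact.** Let d be the four facility changes. The uncorrected sandwich variance of the mean change is Σ(d − mean)² / 16. The paired t-test uses Σ(d − mean)² / 12. The sandwich standard error is therefore √(3/4) of the paired one, and the G/(G−1) = 4/3 correction makes them equal. Hence, under a true null:
- uncorrected, z: P(|t₃| > 1.96 × √0.75) = P(|t₃| > 1.70) = 18.8%
- corrected, z: P(|t₃| > 1.96) = 14.5%
- corrected, t with 3 df: critical value 3.18, 5% by construction

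**3. Simulation, true change zero, nominal 5%.**

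| Analysis | Rejection rate |
|---|---|
| Uncorrected sandwich, z, equal volumes | 18.6% to 19.0% |
| Uncorrected sandwich, z, unequal volumes | 21.2% to 21.7% |
| Corrected sandwich, z | 14.0% to 17.0% |
| GEE robust, z (400 runs each) | 17% to 21% |
| Logistic, corrected sandwich, z | 13% to 16% |
| Facility intercept, model-based, r = 1 / 0.8 / 0.5 / 0, seven births | about 5% / 11% / 18% / 26% to 28% |
| Corrected sandwich, t(3), linear | 4.8% to 6.0% |
| Corrected sandwich, t(3), logistic | 3.7% to 6.1% |
| Paired t-test on facility means, 3 df | 4.8% to 5.3% |

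**4. Power of the paired test, seven births per facility and round.** Between-facility variance: 0.25 × 0.0289 = 0.007225. Within: 0.75 × 0.0289 = 0.021675. Variance of one facility's change: 2 × 0.021675 / 7 + 2 × 0.007225 × (1 − r). The standard error of the mean change is the square root of that variance divided by 2. The noncentral t with 3 df needs a noncentrality of 4.26 for 80% power.

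| r | Variance of change | SE | 0.24 / SE | Power for 24 points | Difference at 80% power (4.26 × SE) |
|---|---|---|---|---|---|
| 1 | 0.00619 | 0.0393 | 6.10 | 97% | 17 points |
| 0.8 | 0.00908 | 0.0477 | 5.04 | 90% | 20 points |
| 0.5 | 0.01342 | 0.0579 | 4.14 | 78% | 25 points |
| 0 | 0.02064 | 0.0718 | 3.34 | 62% | 31 points |

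The plan's formula has no pairing term. With n = 7 its variance is 2 × 0.0289 × (1 + 6 × 0.25) / 7 = 0.02064, which is the r = 0 row. An unpaired t-test on facility means (6 df) has a simulated power of 79.8% in that row, so the formula fits an unpaired test better than a paired one.

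**The case against.** The strongest reply is that the article names no estimator, so any error rate belongs to a method the reader has supplied. The same sentence can be carried out as a corrected sandwich with t(3), which stays near 5%. A facility-intercept model is also near nominal if facility effects are stable. Details of this kind are often left to a full protocol or analysis plan, and neither is shown. This stands, and it limits the claim: a reader might infer that the planned primary test will reject a true null about one time in five, and the article does not support that. For the logistic model the simulated rate with a corrected sandwich and z is nearer one in seven.

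A second reply is that a regression coefficient is itself tested with a t statistic, so the two sections need not conflict. That holds only if the degrees of freedom reflect four facilities and not the number of births, which the Statistical methods section does not say.

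A reader might also infer that the t-test disappears after the sample-size section. It does not. Different women deliver in each round, so births cannot be paired. A paired, weighted test therefore makes most sense on facility averages, close to the remedy below. But the text places it within each facility and makes it additional to the regression, so it does not secure the primary result.

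What remains does not depend on an unseen plan: the article recognises the few-facility problem in one section and fixes its main tests without that safeguard in another.

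**Conclusion.** The point holds as an open risk. It is not a demonstrated error rate. If the regressions are run with normal critical values on a sandwich or GEE variance, type I error is about 14% to 22% (logistic, corrected sandwich: 13% to 16%). With a facility intercept and model-based errors it is about 5% under stable facility effects and 11% to 28% at correlations of 0.8 to 0. With a corrected sandwich and t(3), or a paired test on facility means, it is about 5%. The sandwich figures rest on the number of facilities and barely depend on the ICC or the between-round correlation. The facility-intercept and power figures do depend on that correlation, which the article does not give. The stated detectable difference of 24 points is arithmetically sound for the formula used. Whether it holds for the eventual test depends on which test is chosen.

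**What to change.** Name the overall test in the Statistical methods section. Either of these will do:
- A paired t-test on the four facility-level changes, 3 df, critical value 3.18. If this is what the paired, weighted t-test was meant to be, say so, drop the within-facility wording and make it the main test.
- The delivery-level regression with facility effects and a small-sample-corrected cluster variance referred to t(3), or with a random facility-by-round effect and Satterthwaite or Kenward-Roger degrees of freedom. The facility-by-round term must be random: as a fixed effect it would saturate the facility-round means.

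Treat the 75% endpoint the same way, through facility-level risk differences or a corrected variance with t(3). Sign-flip tests do not help: four facilities give 2⁴ = 16 patterns, so the smallest two-sided p is 2/16 = 0.125.

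Then align the Sample size section with the chosen test, state the assumed between-round correlation, and restate the detectable difference if needed.

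The change is to wording and the power statement; data collection is unaffected. The price is wider intervals (3.18 in place of 1.96). For the paired test, power for 24 points is below the 80% target at correlations of 0.5 and 0, and above it at 0.8 and 1.

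### On the plan's own baseline values the 75%-of-tasks endpoint will more likely than not have no baseline events, in which case ordinary logistic regression cannot give a usable comparison with baseline

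*Protocol article*

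**What the plan says.** The Statistical methods section scores each delivery as a percentage of 21 items and analyses the mean score as the primary outcome. It then adds a dichotomised version, meant to show meaningful change due to the programme: "we will examine if there is an increase in the proportion of births where the majority (75%) of tasks are completed". The model is named: "To this end we will run individual-level logistic regression, accounting for clustering at the facility level". Nothing is said about sparse or empty cells, or about how time enters the model.

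The planning values are in the Sample size section: "We estimate that at baseline 34% (m_0_) of the 15 SCC items will be observed per birth"; "s_0_ and s_1_ are the standard error at baseline (17"%); "ρ = interclass correlation (0.25"); and "we could expect to observe an average of 6.5 (n) deliveries per site". The Data collection methods section sets a floor of three days, or as long as it takes to see seven births, in each of the four facilities.

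**The concern.** The cut-off is far above the baseline level that the plan expects, and each round is small. If no baseline birth reaches 75% and some later births do, every event lies in the later rounds. The data are then quasi-completely separated on the baseline contrast: the maximum-likelihood odds ratio runs to infinity, and its Wald standard error reflects where the software stopped iterating rather than the data.

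The practical risk is a misleading p-value. The same data can appear as no effect or as overwhelming significance, depending on the variance estimator. The Discussion says that the results are to inform plans for adopting the checklist in Zambia, and this is the analysis singled out to show meaningful change. A larger programme effect would not cure the problem, because it comes from the empty baseline cell.

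**Working it through.** **Reproducing the plan's sizing.** Inputs from Sample size: z values 1.96 and 0.84, s0 = s1 = 0.17, ρ = 0.25, n = 6.5, difference 0.24.

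- n = 390 / 4 / 30 × 2 = 6.5 births per site in 48 hours, as stated.
- c = 1 + 2.80² × (2 × 0.17²) × (1 + 5.5 × 0.25) / (6.5 × 0.24²) = 3.87, which rounds up to 4 facilities.
- Solving for c = 4 gives a detectable difference of 23.5 points, against 24 stated.

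The sizing reproduces with 17% used as the between-birth standard deviation (SD), although the text calls it a standard error. The same values are used below.

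**Births per round.** Floor: 4 × 7 = 28. Three days at the stated volume: 390 / 4 / 30 × 3 = 9.75 per site, or 39 in all.

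**Cut-off.** 0.75 × 21 = 15.75, so at least 16 items.

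**Share of baseline births at or above the cut-off.** The document gives no score distribution, so three shapes are assumed, each with mean 0.34 and SD 0.17.

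- Normal: z = (0.75 − 0.34) / 0.17 = 2.41, p = 0.79%.
- Beta: a + b = 0.34 × 0.66 / 0.17² − 1 = 6.76, so a = 2.30, b = 4.46 and p = 1.23%.
- Beta-binomial on 21 items: P(X ≥ 16) = 1.44%.

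**Chance of no baseline event**, (1 − p)^N for independent births:

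| Shape | p | Expected events, N = 28 / 39 | P(none), N = 28 / 39 |
|---|---|---|---|
| Normal | 0.79% | 0.22 / 0.31 | 80% / 73% |
| Beta | 1.23% | 0.34 / 0.48 | 71% / 62% |
| Beta-binomial | 1.44% | 0.40 / 0.56 | 67% / 57% |

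Facility correlation was added by simulation (four sites, correlation 0.25 on a latent normal scale, 60,000 runs). P(none) is then 82% (28 births) and 75% (40 births) for the normal shape, and 73% and 65% for the beta shape. The range over all of these is about 57% to 82%.

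**Later rounds.** At the plan's m1 = 58% with the same SD, 16% (normal), 17% (beta) or 19% (beta-binomial) of births reach the cut-off. That is about 4.4 to 5.3 of 28, so an empty baseline cell would usually face a non-empty later one.

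**What the model then reports.** Illustration: 0/28 at baseline against 5/28 at endline, with the five events split 2, 1, 1, 1 over the facilities.

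- Model-based logistic regression: log odds ratio about 22, standard error about 15,000, p = 0.999.
- Generalised estimating equations (GEE), independence working correlation, cluster-robust: log odds ratio about 24, standard error 0.21, p printed as 0.
- Fisher's exact test, ignoring facility: p = 0.051.

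With 0/28 against 2/28 (events in two facilities), the same GEE fit still prints p as 0, while Fisher's p is 0.49.

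**Sensitivity.** No event stops being the likelier result once p exceeds 1 − 0.5^(1/28) = 2.4% with 28 births, or 1 − 0.5^(1/39) = 1.8% with 39. P(none) for 28 / 39 independent births:

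| Change in assumption | Normal | Beta | Beta-binomial |
|---|---|---|---|
| Mean 0.40, SD 0.17 | 57% / 46% | 51% / 39% | 46% / 34% |
| Mean 0.45, SD 0.17 | 33% / 21% | 30% / 19% | 25% / 14% |
| Mean 0.34, SD 0.20 | 57% / 45% | 41% / 29% | not run |

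With fewer scored items (beta-binomial, mean 0.34, SD 0.17), P(none) is 78% / 70% for 15 items, 56% / 45% for 12, 74% / 66% for 10 and 51% / 39% for 8. It is not monotone, because the whole-number cut-off moves.

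**The case against.** **The failure is narrower than it may look.** A reader might infer complete separation, and that every estimate and cluster-adjusted p-value from this analysis is meaningless. That goes too far. Most endline births would still be non-events, so the separation is quasi-complete and affects only contrasts with baseline. A likelihood-ratio test stays finite, a one-sided profile-likelihood bound exists, and the risk difference can be computed. The midline-endline contrast is also estimable. This stands.

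**The coding of time is open.** There are three rounds, and the article does not say that time is categorical with baseline as reference. With a linear trend there is no separation: an illustrative 0/28, 3/28, 5/28 fitted without clustering gives a log odds ratio of 1.24 per round, standard error 0.60, p = 0.039. This stands, so the point applies to comparisons of a later round with baseline.

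**The inputs are not a forecast for this endpoint.** The 34% was set for 15 items from Indian data on 29, while the outcome has 21 selected items. The Outcomes section also scores tasks out of those observed, which may shorten the denominator. Birth counts are minimums. All of this stands and limits how firmly the probability can be stated; the sensitivity figures show by how much.

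**The analysis is exploratory, and a sparse-data fallback could sit in an analysis plan.** It is indeed not primary and carries no sizing claim. But the article names a model, and the ordinary form of that model fits poorly with the article's own planning values. The article's wording does not exclude a penalised or exact version, so the change is easy to make.

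**Conclusion.** The point holds in a limited form. On the plan's own values, about 1% of baseline births would complete at least 75% of the 21 items. No baseline event is then more likely than not, at roughly 57% to 82%. When that happens and later events occur, the ordinary odds ratio against baseline is infinite, and Wald or cluster-robust standard errors and p-values are unreliable and can disagree wildly.

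This rests on the 34% mean, the 17% read as a between-birth SD, scoring on all 21 items, 28 to 39 births per round, and assumed score shapes. With a true baseline mean of 45% the chance of an empty cell is about 14% to 33%; at 40% it is near or below even.

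A reader might also infer that the analysis fails however it is run, or that the trial's main result is at risk. The documents support neither: usable tests remain, and the mean-score analysis does not depend on this model.

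**What to change.** In Statistical methods, for the 75% endpoint:

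1. Report the number and proportion of births reaching 75% in each round, and the absolute difference from baseline with an exact or score interval.
2. In place of ordinary logistic regression, use Firth-penalised logistic regression with facility as a fixed effect and penalised-likelihood (not Wald) intervals and tests, or an exact test stratified by facility.

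The cost is a change of wording, with no new data. The penalised estimate is slightly shrunk, and the exact test is somewhat conservative. A simple interval for the pooled difference treats births as independent, so it should be presented as descriptive alongside the facility-adjusted result. The primary analysis needs no change on this account.
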